As part of relational wellbeing, *emotion*, *connectedness*, and *rigidity* statements between caregivers and their care-recipients will be assessed *via* an audio-recorded 10-min semi-structured interview. Verbatim transcripts will be prepared and analyzed using a text analysis software Oedipus Text (Ascher et al., 2010; Connelly et al., 2020). We will assess socioemotional language usage in caregivers across three domains (see Supplementary material):

*Emotion*: Consistent with other studies of emotional language usage (positive and negative), a composite list consisting of words from the emotional lexicon state will be used.*Connectedness:* We will identify the number of pronouns in each of the following three lexical categories, as defined by the pronoun lexicon: we-words (pronouns referring to the couple), me-words (pronouns referring to the speaker) and you-words (pronouns referring to the other spouse).*Rigidity*: We will identify the number of rigid statements (e.g., never) regarding the care recipient’s behavior or characteristics, as defined by the rigidity lexicon.

After initial independent scoring, a consensus review will be performed to confirm reliability and validity of scoring for all analyses. For each domain, mean composites will be generated. In addition, exploratory qualitative analysis will be performed to examine themes in all three domains.

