### Data analysis plan

The study will use mixed methods, integrating quantitative and qualitative strategies, making no assumptions about linear relationships between quantitative and qualitative data/findings (DePoy and Gitlin, 1994). These two strategies will be employed as different ways of exploring and understanding the theme in question, i.e., mindfulness and caregiver wellbeing.

Regarding quantitative measures we will first identify factors that are confounders between the two intervention groups, which may include socio-demographics, relationship to care recipients, healthcare access, socioemotional support, dementia patient diagnosis, engagement in intervention, relationship quality with facilitator, hours (weekly) spent with the person with dementia. Any variables showing significant group differences will then be considered confounds and included in the main statistical analyses. We will also check for missing data and signs of systematic response bias in self-reported responses. The main analysis will evaluate the effect of treatment group x time (t0, t1, t2). All participant outcome measures (domains: relational well-being, psychological well-being, dementia patient’s lifestyle changes), will be analyzed using generalized linear mixed models. Models will treat treatment and time points (including their interaction) as fixed effects and caregivers as random effects. We will look for a main treatment effect, a main time effect, and an interaction effect of treatment by time. All hypotheses will be individually evaluated at a nominal *p*-value of 0.05.

Semi-structured interviews will be analyzed using thematic analysis. First, grounded theory’s open coding stage will be employed, followed by axial coding and analyses (Spradley, 1979; Charmaz, 2006). We will identify meaningful themes and conceptualize our findings in relation to existing mindfulness theories and stress reactivity research. Because the first two authors are mindfulness teachers who have worked extensively with older adults, including dementia caregivers, qualitative data will be analyzed separately and jointly by the first two authors. Final synthesis of analyzed data will be obtained through continuous discussions among the research team until consensus is reached.

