### Procedures to reduce bias

Participants will be randomly allocated with 1:1 allocation ratio to one of the two arms *via* a computerized random number, generated *via* the R software (Team, 2014). The numeric random sequence document will be unavailable to the researcher in charge of enrolling and assessing participants, to avoid research bias. Enrollment interviews, consenting, and assignment of group allocation will be performed by research team members other than those who will facilitate the mindfulness-based class or the caregiver support group. Participants and group facilitators cannot be blind to arm allocation due to each intervention’s nature (distinct, identifiable material and procedures). Investigators and instructors have undergone formal training in the reduction of cultural bias in research settings.

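### The protocol states no masking to arm or visit for those who score or code the interviews, and it chooses thematic coders because they are mindfulness teachers

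*Protocol article*

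**What the plan says.** Under Primary outcome: Relational well-being, the article includes a recorded 10-minute semi-structured interview in the primary domain: emotion, connectedness and rigidity "statements between caregivers and their care-recipients will be assessed" from it. Two things are then done with the interviews.

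- **Quantitative scoring.** "Verbatim transcripts will be prepared and analyzed using a text analysis software Oedipus Text", using emotion, pronoun and rigidity lexicons. A human step follows: "After initial independent scoring, a consensus review will be performed to confirm reliability and validity of scoring for all analyses". The scorers are not identified.
- **Thematic analysis.** The same section adds that "exploratory qualitative analysis will be performed to examine themes in all three domains". The Data analysis plan names the coders: "qualitative data will be analyzed separately and jointly by the first two authors". It gives their background as the reason for this choice: "Because the first two authors are mindfulness teachers who have worked extensively with older adults". Their experience is said to extend to people caring for someone with dementia. The team will "conceptualize our findings in relation to existing mindfulness theories and stress reactivity research", and the final synthesis is settled by discussion within the research team.

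On masking, Procedures to reduce bias says only that "Participants and group facilitators cannot be blind to arm allocation", because the two programmes are recognisably different. It also withholds the random sequence from the researcher who enrols and assesses, and keeps class and support-group facilitators out of enrolment, consent and assignment. The recruitment and allocation section states concealment from staff only up to the point of randomization. Data protection says that interview files carry names that do not identify the participant.

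**The concern.** A transcript can be masked even when its speaker cannot. Participants in this trial know their arm, and most outcomes are their own self-report, so the interviews are among the few relational measures where one source of bias, the rater, can be removed.

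The plan does more than leave a detail out. It has a section on reducing bias that discusses masking and does not reach the raters. It also assigns the thematic coding to people whose profession is the method taught in one arm, frames the themes in that method's theory, and resolves them by team discussion. If coders can tell which arm or visit a transcript comes from, a difference in themes between arms may partly be a difference in how they read. The study is meant to inform larger ones, so such a reading would be carried forward.

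**Working it through.** There is no figure in the plan to reproduce, so the check sets the relevant statements side by side.

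**1. Is rater masking stated anywhere?** Three statements come close, and none is stated to hide arm or visit:
- Withholding the random sequence (Procedures to reduce bias) protects the allocation process. It does not address transcripts made at months 2 and 5.
- Concealment from staff (Recruitment, consent, and allocation to interventions) is stated only up to randomization.
- Non-identifying file names (Data protection) hide who the person is. They are not said to omit arm or visit, and they do nothing about a participant who talks about the class, a teacher or a module.

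The separation of facilitators from enrolment, consent and assignment has no stated counterpart for scoring or coding.

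**2. Where could knowledge of the arm enter?** Baseline interviews come before randomization, so their content cannot reveal the arm. Content at months 2 and 5 can. An arm-related shift in scoring prompted by content would therefore appear after baseline only, which is the pattern that the treatment-by-time term in the main analysis is meant to detect.

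**3. How much room is there for rater judgement?**
- *Lexicon scores.* Matching words against a fixed list by software leaves little room. The human scoring and consensus review leave some. The connectedness categories depend on whom a pronoun refers to, and a rigid statement counts only if it concerns the care recipient. Those are plausibly judgements about context.
- *Themes.* Open and axial coding is interpretation throughout, so the room is larger. No statistical test of themes is described, so the harm would be to interpretation and not to a p-value.

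**4. Workload of a remedy.** Transcripts: 40 participants × 3 visits = 120 at most. At an assumed 5 minutes each, 120 × 5 = 600 minutes = 10 hours. At an assumed 10 minutes each, 120 × 10 = 1,200 minutes = 20 hours.

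**The case against.** The strongest reply has four parts.

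- **The primary-domain scores are mostly made by software.** This stands. A reader might infer that the mindfulness teachers produce the primary-domain scores, or that rater bias drives them. The documents support neither: the two authors are named only for the qualitative analysis, and lexicon counts resist allegiance. What remains is the human scoring and consensus step.
- **Silence is not a statement that raters are unmasked.** This also stands. The article is condensed, it refers interview material to a supplement that is not shown, and transcript handling may be described elsewhere. The point is therefore that no masking is stated, not that none will occur. It is still worth raising, because the article addresses masking explicitly and fixes the choice of coders.
- **Expert coders are a legitimate choice, and the work is exploratory.** The article gives a reason: long experience with older adults and dementia caregivers. Coding is done separately as well as jointly, and the wider team is consulted. It would be wrong to say that masking is given up for nothing. But expertise and masking are compatible, since the same people can code relabelled transcripts first.
- **Bias cannot be sized.** Agreed. A reader might want an inflated false-positive rate. That would rest on an assumed rater shift which has no source in the documents, is doubtful for software counts, and has no test to attach to for themes.

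A reader might also infer that the two coders are the instructors of the mindfulness class. The article does not say so.

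**Conclusion.** The point holds in a limited form. The protocol article states no masking to arm or visit for those who score and review the interview language measures, or for the thematic coders, and it selects those coders because they are mindfulness teachers. For the primary-domain scores, the exposure is small and confined to human scoring and consensus. For the exploratory themes it is larger: apparent arm differences could reflect coder allegiance. No numerical size can be given.

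This rests on two assumptions: that no masking procedure is set out in a document not shown, and that post-baseline transcripts sometimes contain cues to the arm. If the first is wrong, a sentence in the article describing the procedure would settle the matter.

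**What to change.** State the following in Procedures to reduce bias and in the Data analysis plan:

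1. Before any scoring or coding, a team member who does neither relabels the transcripts with random IDs that carry no arm or visit, and shuffles them across arms and visits.
2. Scoring and consensus review of the emotion, connectedness and rigidity measures are done on copies in which references to class, teacher and module are masked. The scores are locked before unmasking.
3. Theme coding is first done and recorded on the relabelled transcripts. The unmasked text is consulted only afterwards, for interpretation.
4. Anyone who taught a participant does not score that participant's transcript. This is a conditional safeguard and does not assume that any scorer taught the class.

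The coders' expertise is kept, and participants, visits and interventions are unaffected. The cost is about 10 to 20 hours of existing staff time on the assumption above. The drawbacks are some residual unmasking from what participants say, and some loss of context during masked coding, which step 3 partly restores.

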### Fidelity of implementation

Quality of the mindfulness-based intervention will be ensured through the engagement of two certified MBSR instructors with experience in practicing and teaching mindfulness *via* Zoom. These two instructors will co-lead each session and will undergo weekly debriefing with the study lead (a clinical psychologist) and their MBSR supervisor to resolve any implementation issues.

### Strategies for improving adherence

Throughout the study, participation in both arms will be monitored, and retention enhanced *via* emails and calls. In the mindfulness-based intervention participants attending at least five of eight sessions will be defined as completers and will be included in the final analysis, though the number of completed sessions will be evaluated as a potential confound. To document participants’ daily mindfulness practice throughout the course, a weekly online survey will be employed accounting for home practice frequency and quality. In the active control arm, participants’ progress and skill completion can be monitored online by study staff; participants completing 75% of the material before the T1 assessment and attending at least one in-person session will be included in the final analysis, though different levels of completion will be evaluated as a potential confound.

Interventions may be discontinued at the participant’s request, with case-by-case evaluation of causative factors (e.g., death of care-recipient, acute trauma, intense amount of stress/grief, scheduling conflict). Any participant not meeting the preset participation thresholds will not be excluded from completing the remainder of the study, but their data will not be analyzed. Some attrition is expected, but with enhanced retention *via* direct contact with participants, we believe we can retain 80% of participants through the entire intervention and T1 assessment.

While we suggest a fairly broad array of assessment measures in this protocol, the overall time to complete them is ~1 h. In our two decades of experience performing observational research with caregivers of dementia patients, we have found that 1 h of questionnaires is not typically experienced as unduly burdensome for these individuals. However, individuals with more extreme current stressors could find the time demand for participation in the protocol daunting, thus they are fully informed of the demands on their effort during the informed consent process, at which time they will have the option to decline to participate.

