### Recruitment, consent, and allocation to interventions

Participants will be recruited by local advertisements and recruitment talks in the San Francisco Bay Area, online dementia caregiving groups, and by accessing an established research registry database. Recruitment is planned to continue until 40 eligible participants are enrolled (20 per intervention arm), and the approximate recruitment period is 2 months. Participants will not receive financial compensation for taking part in the study, and there will be no inducements for completing interventions. Participants deemed suitable for recruitment, will be contacted *via* email or phone with an opportunity to participate in additional eligibility screening, and to complete an online screening questionnaire to confirm eligibility. A follow-up email will include a review of study details (e.g., start date, expectations).

All screening and recruitment conversations will be completed by research personnel trained in the ethical conduct of human subjects’ research. Informed written consent will be obtained *via* interview with a trained examiner (*via* Zoom), during which the study will be clearly explained in detail, and caregivers will be able to ask questions prior to enrollment. Caregivers will also be informed that they can drop out of the study at any time. After this conversation, those agreeing to participate will be asked to formally consent to study participation. Due to current pandemic restrictions, DocuSign will be used to obtain participants’ consent signatures electronically. The amount of time expected for this consenting process is 20 min.

Next, for the baseline assessment part of the study (T0, 0 months), enrolled participants will be scheduled to participate in a 10-min semi-structured online interview *via* Zoom (see Supplementary material) and will complete a set of online surveys and performance tasks *via* Qualtrics. Those evaluations are designed to minimize possible subject fatigue, stress, and boredom. Breaks from testing will be allowed, and testing sessions may also be broken into multiple sessions. After all participants have completed enrollment and baseline assessment, they will be randomized to one of the two study arms and will then be informed *via* email of the group to which they have been assigned (see Figure 1; Table 1).

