#### Active control group (self-guided program)

Caregivers allocated to this study arm will be assigned to a self-guided, online, weekly program that specifically targets positive emotion (Cheung et al., 2018; Addington et al., 2019; Moskowitz et al., 2019). The material aims to cultivate skills such as positive reappraisal, gratitude, self-compassion, and setting manageable goals. The program consists of skills introduced gradually over a 6-week period that caregivers will learn about and practice independently. Caregivers will also be asked to complete a daily questionnaire recording their feelings. To better mimic the structure of the active MBSR arm, which is in-person weekly, participants in this control arm will also be asked to participate in two online, interactive group discussions with other caregivers (*via* Zoom) at Week 4 and Week 8, facilitated by the study’s research director. This component will provide a space for caregivers to interact in person with others and discuss stressful experiences and application of skills learned to daily caregiving challenges. Study personnel are able to monitor the degree of completion of each module and will communicate with any caregiver who seems to be falling behind or otherwise not completing the work.

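### The final analysis drops randomised participants who miss arm-specific participation thresholds, which can bias the between-arm effect sizes; no all-randomised analysis is stated

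*Protocol article*

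**What the plan says.** Allocation comes before any participation can be observed. Under Recruitment, consent, and allocation to interventions: "After all participants have completed enrollment and baseline assessment, they will be randomized to one of the two study arms".

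Strategies for improving adherence then defines who is analysed.
- Mindfulness arm: "participants attending at least five of eight sessions will be defined as completers and will be included in the final analysis".
- Control arm: "participants completing 75% of the material before the T1 assessment and attending at least one in-person session will be included in the final analysis". The section on the active control group offers "two online, interactive group discussions with other caregivers", at Weeks 4 and 8, so the attendance part of this rule is read here as one of those two.
- Anyone below threshold: "will not be excluded from completing the remainder of the study, but their data will not be analyzed".

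The same section says, for each arm, that the amount completed will be evaluated as a potential confounder. The Data analysis plan lists engagement in the intervention among the candidate confounders. It names no analysis set; its opening reference to all outcome measures concerns measures, not all randomised people.

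**The concern.** Randomisation makes the arms comparable at the start, and that protection covers the groups as randomised. Here membership of the analysis set is decided by behaviour during the programme, under a different rule in each arm, among participants who know their allocation (Procedures to reduce bias). If the caregivers removed differ in outcome from those kept, and differ in another way or number in the other arm, a between-arm difference can appear with no treatment effect, or a real one can be distorted.

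What is at stake is the study's stated product. The Sample size calculation says the study will establish preliminary effect sizes for all measures, and the Discussion says it will inform larger studies. An effect size distorted by selection would carry over into their planning.

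**Working it through.** **The plan's own figures.** The documents give neither the share expected to meet each threshold nor the correlation between adherence and outcome. There is no stated figure to reproduce, and everything below about size is illustration.

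**Step 1: the rules side by side.**

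| | Mindfulness | Control |
|---|---|---|
| Format | live weekly class | self-guided material plus two group discussions |
| Threshold | 5 of 8 sessions (5/8 = 62.5%) | 75% of material before T1, and at least 1 of 2 discussions |
| Below threshold | may continue, not analysed | may continue, not analysed |

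The rules differ in kind as well as level, so equal selection in the two arms cannot be taken for granted.

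**Step 2: shift within one arm.** Suppose a latent normal adherence score has correlation c with the outcome (outcome SD = 1, no treatment effect), and the lowest fraction p is excluded. The mean among those kept shifts by c·k(p), where k(p) = φ(z_p)/(1−p).
- k(0.10) = 0.1755/0.90 = 0.195
- k(0.20) = 0.27996/0.80 = 0.350
- k(0.30) = 0.3477/0.70 = 0.497

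**Step 3: spurious arm difference.** This is c_M·k(p_M) − c_C·k(p_C), with M for mindfulness and C for control. All inputs are assumed.

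| Excluded M / C | c_M / c_C | Difference (SD) |
|---|---|---|
| 20% / 20% | 0.4 / 0.4 | 0 |
| 20% / 20% | 0.3 / 0 | 0.3 × 0.350 = 0.105 |
| 20% / 20% | 0.5 / 0 | 0.5 × 0.350 = 0.175 |
| 30% / 10% | 0.3 / 0.3 | 0.3 × (0.497 − 0.195) = 0.09 |
| 30% / 10% | 0.5 / 0.5 | 0.5 × 0.302 = 0.15 |
| 30% / 10% | 0.5 / 0 | 0.5 × 0.497 = 0.25 |

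The sign reverses if the heavier selection falls in the control arm.

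**Step 4: simulation check.** 5,000 runs, 20 per arm randomised, no true effect, two-sided t-test at 0.05.

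| Completion M / C | c_M / c_C | Bias (SD) | Type I error, completers |
|---|---|---|---|
| 80% / 80% | 0.4 / 0.4 | −0.01 | 4.7% |
| 80% / 60% | 0.4 / 0.4 | −0.12 | 6.5% |
| 70% / 90% | 0.4 / 0.4 | 0.13 | 6.6% |
| 80% / 80% | 0.5 / 0 | 0.18 | 7.4% |
| 70% / 90% | 0.5 / 0 | 0.25 | 10.2% |

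Analysing everyone randomised gave 4.7% to 5.6% across the scenarios run.

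**Step 5: the planned contrast.** Steps 2 to 4 concern a single outcome score. The Data analysis plan makes treatment by time the main effect of interest. For the change from T0 to T1, let c0 and c1 be the correlations of adherence with the outcome at T0 and T1. One arm's contribution to the bias is then (c1 − c0)·k(p). If adherence tracks only a stable level of strain, c1 = c0 and the contribution is zero. Bias remains where non-completion is related to change. The main treatment effect, which the plan will also examine, is exposed to the full shift.

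**Step 6: the plan's safeguard.** Sessions attended and material completed arise after allocation and are measured on different scales in the two arms. Adjusting for them among completers neither brings back the people removed nor restores the randomised comparison.

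**The case against.** The strongest reply is that this is a disclosed exploratory pilot whose imprecision exceeds the bias. With 16 per arm the standard error of a difference is about √(2/16) = 0.35 SD, against an illustrated bias of 0.09 to 0.25 SD. That stands as a limit on severity. It does not make the rule sound: the plan tests hypotheses at 0.05 and offers its effect sizes to later trials, and a larger sample would shrink the standard error but not the bias.

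It can also be said that a completer definition must be arm-specific when formats differ this much. That stands too. The gap between 62.5% and 75% is no defect in itself; the fault lies in using the thresholds to define the only analysis.

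An unseen analysis plan is no answer, because the exclusion is stated positively and an all-randomised analysis would contradict it.

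Three stronger readings should be resisted.
- A reader might infer that the bias is certain and favours mindfulness because strained caregivers miss live classes. The documents do not say so. The reasons given for stopping apply to both programmes and include a scheduling conflict as well as grief and trauma.
- A reader might infer that the rule cuts the sample from 40 to 32 (80% of 40). That 80% is expected retention through the intervention and T1. People lost before T1 would have no T1 value under any analysis.
- A reader might infer that the excluded participants' T1 and T2 data will all be in hand. They are permitted to continue, which does not mean that all will.

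**Conclusion.** The point holds. The protocol states a rule that replaces the randomised comparison with one between completers selected differently in each arm, and it provides no analysis of everyone randomised. The rule can bias the between-arm effect sizes. Whether it does, in which direction and by how much cannot be derived from the documents. The illustrated range of about 0.09 to 0.25 SD rests on assumed exclusion of 10% to 30% and on adherence–outcome correlations of 0 to 0.5 that differ in size or effect between arms; with the same selection in both arms the bias is about nil. For the treatment-by-time contrast it applies only as far as non-completion is related to change. The rule also discards usable data from anyone who falls short but is still assessed, in a number the documents do not give.

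**What to change.** Make the primary analysis all randomised participants in their assigned arm, using every available T0, T1 and T2 value in the planned mixed model whatever the participation. Actively invite those who stop the programme to the T1 and T2 assessments. Replace the sentence that leaves their data unanalysed with a secondary completer (per-protocol) analysis using the two existing thresholds, and examine completion level there.

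The cost is a change of wording and a little follow-up effort. Values will still be missing for those who do not return, so the mixed model's missing-at-random assumption remains. The estimated effect will probably be somewhat smaller than among completers, because it describes assignment to the programme, not completion of it.
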